### **3.7.4 Subgroup analyses**

Subgroup analyses to account for the impact of flooding will be conducted as described above.

Subgroup analyses will be conducted separately for each of the following variables: LGA location (metropolitan vs rural), age group (18 to < 45, 45 to <65, 65+), sex, country of birth (Australia vs Other), priority postcodes (priority vs non-priority postcodes), and ACS subtype (acute myocardial infarction vs unstable angina). Terms for these variables will be included in each of the primary analysis models, together with an interaction with

the intervention indicator. Estimates and 95% confidence intervals for the intervention effects for each subgroup, together with the p-value of the interaction term, will be reported.

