- Awareness of heart attack/heart disease as the leading cause of death (the proportion who identify heart attack/disease as a leading cause of death in men/women to be compared between groups)
- Awareness of heart disease (cardiovascular) risk factors (the proportion who correctly identify any cardiovascular risk factor as increasing their risk of heart disease to be compared between groups)
- The number of correctly named heart disease (cardiovascular) risk factors (the mean number of correctly named cardiovascular risk factors to be compared between groups)
- Awareness of heart attack signs and symptoms (the proportion aware of any heart attack symptom[7] to be compared between groups)
- The number of correctly named heart attack signs and symptoms (the mean number of correctly named heart attack symptoms[7] to be compared between groups)
- Confidence in knowing how to act (the proportion very confident/confident about what they would do if experiencing a heart attack to be compared between groups)
- EMS use in severe chest pain scenario (the proportion who state they would call EMS to be compared between groups)
- EMS use in chest discomfort scenario (the proportion who state they would call EMS to be compared between groups)

The following will be obtained from Medicare:

- The number of Heart Health Checks (numbers of Medicare claims for Heart Health Checks, items 699/177) by LGA and month. The number of adults eligible for Medicare in each LGA will allow analysis of this as a rate for each LGA in each month.

The following will be obtained from the VEMD:

- Number of ACS emergency department presentations (numbers of ED presentations that have a final ED diagnosis of ACS[10]), by LGA and month. Adult population sizes of LGAs will be obtained from the Australian Bureau of Statistics to allow analysis of this as a rate for each LGA in each month.
- Number of emergency department presentations that are for unspecified chest pain (the number of ED presentations that have a final ED diagnosis of unspecified chest pain[10]), by LGA and month. Adult population sizes of LGAs will be obtained from the Australian Bureau of Statistics to convert this to a rate for each LGA in each month.
- ACS ED presentations via General Practitioners (the proportion of ACS ED presentations referred to ED by General Practitioners to be compared between groups)

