#### 3.6.2 *Patient characteristics*

The number of patients admitted to EDs for ACS will be presented by LGA and study period. The characteristics of patients admitted to EDs for ACS will be summarised as counts and percentages (for discrete characteristics), means and standard deviations (for characteristics with approximately symmetric distributions), or medians and interquartile ranges (for characteristics with skewed distributions). Baseline characteristics will be summarised by intervention group (control vs education intervention) and by LGA and study period. Clustering will not be adjusted for in the presentation of patient characteristics. The following patient characteristics will be summarized and presented:

- Age group
- Sex at birth
- Indigenous status
- Living arrangements
- Country of birth (Australian, other English-speaking, non-English-speaking)
- Preferred language English
- Interpreter required
- ACS sub-type

The characteristics of participants responding to the Heart Watch public survey will be summarised by intervention group, data collection round and local government area. Clustering will not be adjusted for, and the following characteristics will be summarized and presented (in the manner described for patient characteristics above):

- Age group
- Sex
- Indigenous status
- Speaks another language other than English at home
- Highest level of education
- Living arrangements
- Working status
- EMS insurance
- Self-reported medical history

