### **3.7.3 Adjusted analyses**

Since there may be imbalances between the LGAs with respect to various patient-level baseline characteristics, the analyses described in Section 3.7.1 will be repeated including patient characteristics that are known to influence EMS use that are available in the VEMD: age, sex, Australian-born, interpreter required, living arrangements, and ACS sub-type.[10] In the case of non-convergence or collinearity, covariates may be examined for collinearity and sequentially removed from the model until convergence is achieved.

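### ACS sub-type is very probably recorded after exposure and after mode of arrival, yet the SAP adjusts for it as a baseline characteristic and tests it as an effect modifier

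*Supplement*

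**What the plan says.** The SAP uses ACS sub-type in three ways.

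- **Description.** Section 3.6.2 includes it among the patient characteristics to be tabulated: "Baseline characteristics will be summarised by intervention group (control vs education intervention"), and also by LGA and study period. The shell of SAP Table 3 has rows for infarction and unstable angina, by control and campaign.
- **Adjustment.** Section 3.7.3 gives its reason as "Since there may be imbalances between the LGAs with respect to various patient-level baseline characteristics", and its covariates are "age, sex, Australian-born, interpreter required, living arrangements, and ACS sub-type". It describes them as available in the VEMD and known to influence EMS use.
- **Effect modification.** Section 3.7.4 ends its list of subgroups with "and ACS subtype (acute myocardial infarction vs unstable angina"), and says how each is tested: "Terms for these variables will be included in each of the primary analysis models, together with an interaction with" the intervention indicator. Subgroup estimates and the interaction p-value are reported, and Figures 3 and 4 repeat them as forest plots. Section 3.1.2 plans no multiplicity adjustment.

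On the source of the label, section 2.5.2 defines the VEMD count of ACS presentations as "numbers of ED presentations that have a final ED diagnosis of ACS". The protocol's description of the VEMD says that ED staff collect the data. The SAP does not state in so many words that sub-type is taken from the same final diagnosis, but the documents point to no other source. The main analysis in 3.7.1 does not use sub-type.

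**The concern.** The other patient-level subgroups (age, sex, country of birth, priority postcode) describe the person before symptoms begin. Sub-type does not. It is a label given in the ED, after the patient has or has not been exposed to the campaign, has decided how to respond, and has arrived by ambulance or otherwise.

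The trial's own objectives give routes by which the campaign could shift that label. The protocol aims to shorten patient and prehospital delay, which may alter the stage of illness at assessment. It also expects more ED presentations for ACS and unspecified chest pain, which may alter who is in each group. Mode of arrival could matter too: the protocol's background says that paramedics detect and treat ACS and that ambulance transport takes suspected cases to hospitals with revascularisation capability, so it may determine which ED makes the diagnosis.

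If the label moves, each sub-type contains different kinds of patients under control and under intervention. A difference between the sub-type effects could then be read as the campaign working in one form of ACS and not in the other, when nobody's ambulance use has changed.

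**Working it through.** **The plan's own figures.** 8 LGAs × 7 analysed periods × 40 patients = 2240, as SAP 2.8 states. With ICC 0.09, fixed period effects, the transition cells dropped and a normal approximation, power for 61% to 72% is 79.4% (variance 0.61 × 0.39), 81.9% (pooled variance) or 82.4% (average of the two variances). This agrees with the stated 80%, so the layout used below is the planned one.

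**Inputs.** The 61% overall EMS use is from SAP 2.8. The sub-type split, EMS use by sub-type and the amount of relabelling are not in the documents. Assumed: 1,000 ACS patients, 700 infarction with 64.3% EMS (450.1) and 300 unstable angina with 53.3% EMS (159.9). Check: 450.1 + 159.9 = 610, or 61%.

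**Step 1: relabelling with no change in arrival mode.** Under intervention, k patients move from infarction to unstable angina, and a fraction s of them came by EMS.

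- Infarction: (450.1 − s·k)/(700 − k)
- Unstable angina: (159.9 + s·k)/(300 + k)
- Overall: 610/1000 throughout, so the true effect is zero.

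| s | k | Infarction effect (points) | Unstable angina effect (points) | False gap (points) |
|---|---|---|---|---|
| 1 (all EMS) | 10 | −0.52 | +1.51 | 2.0 |
| 1 | 20 | −1.05 | +2.92 | 4.0 |
| 1 | 30 | −1.60 | +4.25 | 5.8 |
| 0.8 | 10 | −0.23 | +0.86 | 1.1 |
| 0.8 | 20 | −0.46 | +1.67 | 2.1 |
| 0.8 | 30 | −0.70 | +2.43 | 3.1 |
| 0.643 (infarction group's rate) | 10 | 0 | +0.35 | 0.35 |
| 0.643 | 20 | 0 | +0.69 | 0.7 |
| 0.643 | 30 | 0 | +1.00 | 1.0 |

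The link between labelling and arrival mode (s) drives the result.

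**Step 2: the opposite direction.** Assume 70% infarction and EMS use of 64% against 54%, and move 5%, 10% or 20% of unstable-angina cases to infarction (1.5%, 3% or 6% of all ACS patients). If all those moved came by EMS, infarction appears ahead by 3.2, 6.6 or 14.3 points. If they are moved at random with respect to EMS, unstable angina appears ahead by only 0.2 to 0.8 points. Over infarction shares of 60 to 70%, EMS gaps of 10 to 20 points and 5 to 30% relabelled, the gap is 3.2 to 27.0 points in the first case and 0.2 to 3.3 points, with the opposite sign, in the second.

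**Step 3: false rejection of the interaction test.** There were 400 simulated trials per scenario in the planned layout, direction as in step 2, with no behavioural effect. The model had LGA and period effects, intervention, sub-type and their interaction, on the linear probability scale.

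| Scenario | Interaction rejected at 5% |
|---|---|
| No relabelling | 5.5% |
| 20% relabelled at random | 5.5% |
| 5% relabelled, all EMS users | 12% |
| 10% relabelled, all EMS users | 27% |
| 20% relabelled, all EMS users | 86% |
| Drift to 20% over calendar time in all LGAs, all EMS users, unrelated to the campaign | 30% |

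The drift scenario gave a mean false gap of 7.1 points, because 3.7.4 states no period-by-sub-type term. The linear model stands in for the planned identity-link mixed model and the LGA effect was modest (SD 5 points), so these rates are indicative.

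**Step 4: the overall estimate.** The unadjusted effect stayed near zero in every scenario. The largest shift from adjusting for sub-type was at 20% EMS-linked relabelling: from −0.2 to −1.2 points, a move of 1.0.

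**Step 5: a true shift in case mix.** With the step 1 inputs, let unstable-angina presentations rise by 10%, 20% or 30% at an unchanged 53.3% EMS rate. Overall EMS use becomes (610 + 15.99)/1030 = 60.8%, (610 + 31.98)/1060 = 60.6% or (610 + 47.97)/1090 = 60.4%. The unadjusted effect is −0.2, −0.4 or −0.6 points, while both within-sub-type effects remain zero. Here adjustment for sub-type removes a distortion.

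**The case against.** The best reply is that the large figures need an extreme: every relabelled patient must have come by EMS. This stands. With relabelled patients at the infarction group's own EMS rate, the gap falls to about one sixth, and random relabelling did not raise the false rejection rate.

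Second, the documents support the timing of the label but not the mechanism. No passage says that earlier arrival or ambulance transport changes whether infarction or unstable angina is recorded. That also stands. A reader might infer that sub-type has been shown to be a consequence of the campaign, or that the artefact would favour unstable angina. The documents support neither: the sign reverses with the direction of relabelling.

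Third, a reader might conclude that sub-type should be struck from 3.7.3. Step 5 argues against this. If the campaign truly brings in more unstable angina, adjustment helps; removal would trade one possible bias for another.

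Fourth, it would be wrong to say that the SAP plans no look at the mix. Section 3.6.2 and Table 3 already tabulate sub-type by condition, and 3.6.2 also by LGA and period. What is missing is a comparison adjusted for period. In a stepped wedge, intervention time falls later than control time, so crude shares by condition mix calendar change with any campaign effect.

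The objection does not remove the central point. That infarction and angina differ clinically does not make the recorded label a baseline variable, and neither does its ability to predict EMS use.

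**Conclusion.** The concern holds in a limited form. Sub-type is very probably fixed after exposure and after the primary outcome, and the SAP handles it as a baseline characteristic and a formal effect modifier without saying so. Its interaction test can reject falsely when labelling is linked to arrival mode. With 1 to 3% of ACS patients relabelled from infarction to unstable angina, the false gap runs from about 0.35 to 1.0 points at the infarction group's EMS rate to 2.0 to 5.8 points if all those relabelled are EMS users. These figures rest on an assumed sub-type split, assumed EMS rates and an assumed amount of relabelling; they show what could happen, not what is expected.

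A reader might infer that the primary result is compromised. This mechanism does not support that: relabelling between sub-types leaves the overall proportion unchanged and 3.7.1 does not use sub-type. In the adjusted analysis the shift was about 1 point at most in the scenarios tested, against a target difference of 11 points. The exposure lies in the subgroup result and its interpretation.

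**What to change.** - **3.7.4:** keep the sub-type results as descriptive, label them as defined after exposure, and omit the interaction p-value, also in Figures 3 and 4.
- **3.6.2 and Table 3:** add a period-adjusted comparison of the infarction share between control and intervention conditions, for example with the marginal logistic model of 3.7.1 and infarction as the response.
- **3.7.3:** report the adjusted estimate both with and without sub-type, and stop calling sub-type a baseline characteristic.

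The cost is SAP wording, one planned subgroup that loses its formal test, one extra adjusted model and one extra comparison of the mix. No new data are needed, and the analysis in 3.7.1 is unchanged.

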### **3.7.5 Analysis of time-on-treatment**

To investigate whether the effect of the education campaign changed over time, the analysis in Section 3.7.1 will be repeated including separate terms for each duration of time that the intervention was implemented. Separate estimates of the effect of the intervention for each of these durations will be obtained.

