Results from the trial will be reported according to the CONSORT extension for stepped wedge cluster randomised designs. LGA and patient demographics will be described by LGA and period. All available primary and secondary outcomes will be analysed at the patient level using mixed-effects logistic regression models with a random intercept for cluster and fixed effects for each period and for the intervention. The Kenward-Roger correction will be applied to adjust for the small number of LGAs. Since there may be imbalance between the LGAs with respect to various baseline characteristics, in a secondary analysis we will adjust for potential confounders known to influence ambulance use that are available in the VEMD (e.g. age, sex, Australian born). Estimated effects will be expressed as odds ratios and as risk differences, with 95% confidence intervals. A secondary analysis will include an interaction between time and treatment to investigate a cumulative effect of the intervention over time. It has been shown that misspecification of the within-cluster correlation structure can lead to confidence intervals of incorrect widths, so sensitivity analyses allowing for more complex within-cluster correlation structures will be considered. Analyses will be conducted in Stata and/or SAS as appropriate.

We will also perform subgroup analyses (e.g. age, sex, country of birth) across the primary and secondary outcomes.

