## 2.8 Sample size

The stepped wedge design in the schematic (a six-sequence stepped wedge design, with an implementation period and two clusters assigned to the first and last sequences) will give 80% power to detect a change in the proportion of ACS patients in the eight LGAs arriving via EMS by 11%[10, 12] from a baseline of 61% to 72%, with a two-sided significance level of 5%. This detectable difference depends on an average of 40 ACS patients admitted per LGA in each two-month period (i.e. a total of 2240 ACS patients) and on the intra-cluster correlation, estimated to be 0.09 using data from the Victorian Emergency Minimum Dataset (VEMD) (2011-2015). This data indicated that more complex correlation structures, with decaying correlations over time, were unnecessary. The Stepped Wedge Stata Program was used for the sample size calculation,[13] verified using the Shiny CRT app.[14] No adjustment was made for LGA or participant attrition, as health services routinely collect the outcomes.

A sample size calculation was also conducted for two online surveys to determine a change in the level of knowledge of ACS symptoms. An online survey in 2020,[7] showed 25% of adults in the intervention LGAs (20% state-wide) could not name any heart attack symptoms. To detect a change from 25% to 10%, with 80% power and 2-sided significance level, requires a survey of 72 adults in each LGA in months 1-2 and again in months 9-10, assuming an intracluster correlation of 0.1, and a cluster autocorrelation of 0.9.

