**Table 8. Analysis of primary outcome, assuming different treatment effects for each number of periods on treatment.**

| Periods
on
treatment | Control n/N
(%) | Education
campaign
n/N(%) | Risk difference
(95% CI) | P     | Odds ratio (95%
CI)    | P     |
|----------------------------|--------------------|---------------------------------|-----------------------------|-------|---------------------------|-------|
| 1                          | n/N (%)            | n/N (%)                         | xx.xx (xx.xx to
xx.xx)   | 0.xxx | xx.xx (xx.xx to
xx.xx) | 0.xxx |
| 2                          | n/N (%)            | n/N (%)                         | xx.xx (xx.xx to
xx.xx)   | 0.xxx | xx.xx (xx.xx to
xx.xx) | 0.xxx |
| 3                          | n/N (%)            | n/N (%)                         | xx.xx (xx.xx to
xx.xx)   | 0.xxx | xx.xx (xx.xx to
xx.xx) | 0.xxx |
| 4                          | n/N (%)            | n/N (%)                         | xx.xx (xx.xx to
xx.xx)   | 0.xxx | xx.xx (xx.xx to
xx.xx) | 0.xxx |
| 5                          | n/N (%)            | n/N (%)                         | xx.xx (xx.xx to
xx.xx)   | 0.xxx | xx.xx (xx.xx to
xx.xx) | 0.xxx |
| 6                          | n/N (%)            | n/N (%)                         | xx.xx (xx.xx to
xx.xx)   | 0.xxx | xx.xx (xx.xx to
xx.xx) | 0.xxx |

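### The time-on-treatment analysis asks whether the effect changed with duration, but plans six row-wise p-values and no comparison between durations

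*Supplement*

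**What the plan says.** SAP 3.7.5 gives its purpose as finding out whether the effect of the campaign changed over time. It refits the 3.7.1 models with one term per duration of implementation, and then: "Separate estimates of the effect of the intervention for each of these durations will be obtained". Nothing further is specified.

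Table 8, titled "Analysis of primary outcome, assuming different treatment effects for each number of periods on treatment", has rows for 1 to 6 periods. Each row carries a risk difference with confidence interval and P, and an odds ratio with confidence interval and P. No row or column compares durations.

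The amended protocol, under its statistical methods heading, says: "A secondary analysis will include an interaction between time and treatment to investigate a cumulative effect of the intervention over time". It does not give the form of that interaction or name a test.

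Elsewhere the SAP does ask for the comparison. Sections 3.4 (flooding) and 3.7.4 (subgroups) both require the p-value of the interaction term, and Table 7 reserves a cell for it under flooding. Section 3.1.2 plans 95% confidence intervals and p-values without multiplicity adjustment.

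**The concern.** The null that matches the stated question is that the six duration effects are equal. The SAP does not state the null behind each P in Table 8, but the natural reading is zero effect at that duration, which is a different hypothesis. Six answers to that hypothesis do not add up to an answer about change.

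The rows also differ greatly in precision. Duration 1 is observed in all eight LGAs; duration 6 is observed only in the two LGAs of the first sequence, in the last period. A constant effect will therefore tend to be significant in the early rows and not in the late ones. Whether community education fades or accumulates is what readers will look for in this table, and the plan gives the authors no prespecified statistic on which to base the statement.

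**Working it through.** **Inputs (SAP 2.8, schematic, Table 1).** Eight LGAs, eight two-month periods, sequences of size 2, 1, 1, 1, 1, 2, and one excluded transition cell per LGA: 64 − 8 = 56 analysed cells. With 40 patients per cell, 56 × 40 = 2240, as the SAP states. Baseline 61%, target 72%, two-sided 5%, "intra-cluster correlation, estimated to be 0.09", and no decay of correlation over time.

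**Model.** Linear approximation to the 3.7.1 risk-difference model: fixed period effects and a random LGA intercept. Total variance 0.61 × 0.39 = 0.2379; between-LGA variance 0.09 × 0.2379 = 0.0214; sampling variance of a cell mean 0.91 × 0.2379 / 40 = 0.0054. The covariance of the effects is the matching block of (X′V⁻¹X)⁻¹.

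**The plan's own figure first.** With a single intervention term, SE = 0.0396. Power = Φ(0.11/0.0396 − 1.96) = Φ(0.82) = 79.4%, against the stated 80%.

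**Six duration terms.** Analysed active cells number 8 + 6 + 5 + 4 + 3 + 2 = 28. Durations 5 and 6 occur only in T7 and T8. Neither period has an analysed control cell, because the last two LGAs are in transition in T7 and active in T8.

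| Active periods | Cells | SE (points) | Chance of p<0.05 at a true 11 points |
|---|---|---|---|
| 1 | 8 | 4.6 | 67% |
| 2 | 6 | 5.3 | 54% |
| 3 | 5 | 6.3 | 42% |
| 4 | 4 | 7.4 | 32% |
| 5 | 3 | 9.1 | 23% |
| 6 | 2 | 10.5 | 18% |

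For example, duration 6: Φ(0.11/0.1051 − 1.96) = Φ(−0.91) = 18%.

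**Joint behaviour under a constant 11-point effect** (400,000 draws from the joint normal distribution of the six estimates):

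| Pattern | Normal critical value | t with 6 df |
|---|---|---|
| Some rows significant, some not, in any order | 69% | 56% |
| No row significant | 22% | 41% |
| All six significant | 9% | 3% |
| Duration 1 significant, duration 6 not | 50% | 41% |
| Duration 6 significant, duration 1 not | under 1% | under 1% |
| Clean fade (significant up to some duration, then not) | 37% | 31% |

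**Sensitivity of the 69%.** Other variance conventions give 66% to 70% with normal critical values and 65% to 70% with 30 to 42 df; 6 df gives 52% to 59%. At a smaller constant effect, with normal critical values, it is 52% for 8 points and 32% for 5 points.

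**Tests of the stated question.** The 5-df test of equal duration effects and the 1-df trend test each reject in 5% of trials under a constant effect. Fitting a line to the six estimates by generalised least squares gives a slope SE of about 1.38 points per period. If the effect grows in proportion to duration:

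- to 11 points at six periods: slope 11/6 = 1.83, ratio 1.32, trend power 26%; 5-df power 14%;
- to 22 points at six periods: slope 22/6 = 3.67, ratio 2.65, trend power 75%; 5-df power 50%.

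**The case against.** The SAP promises estimates and contains no rule for declaring change from which rows cross 0.05. Table 8 gives confidence intervals whose widening is visible. Under a constant effect the duration-6 estimate falls below the duration-1 estimate in 50% of trials, so the estimates have no tilt towards fading. All of that stands: the harm arises only if the p-values are read row by row. The intervals do not replace a comparison, however. The estimates are strongly correlated (about 0.66 between durations 1 and 6), so the uncertainty of a difference cannot be read from two separate intervals.

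Two stronger readings are tempting and are not supported.

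- A reader might infer that under a constant effect the table will most likely look like a fading effect. The 69% counts any mix in any order. A clean fade occurs in 37%, and early-significant with late-not in about 50%, or 41% with 6 df. The plan applies Kenward-Roger but states no degrees of freedom, so the lower figures cannot be ruled out.
- A reader might infer that the SAP replaced the protocol's interaction. Separate terms for each duration are a saturated form of a treatment-by-exposure-time interaction, and SAP 3.5 does not mention withdrawing it. What is missing is a test, which the protocol did not define and the SAP did not add.

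It is also fair that the suggested tests have modest power, and that a non-significant result could be misread as proof of no change.

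**Conclusion.** The point holds in limited form. Section 3.7.5 states a question about change and plans no test of it, while the planned p-values most naturally address another null. They lean in a predictable direction: under a constant 11-point effect, duration 1 significant with duration 6 not is far more common (41% to 50%) than the reverse (under 1%).

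The figures rest on a linear approximation to the risk-difference model, equal cells of 40, ICC 0.09 with exchangeable correlation, and p-values that test zero effect. The odds-ratio p-values were not simulated. The exact percentages move with these assumptions; the rise in standard error with duration comes from the design. Only this secondary analysis is affected, not the primary estimate, test or conclusion.

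**What to change.** In 3.7.5, prespecify one test of the stated question within the 3.7.1 risk-difference model: the intervention term plus a linear term in number of active periods. Report the change in risk difference per period with its 95% confidence interval and p-value, and add a line for it in Table 8. Give the 5-df test that the six duration effects are equal as a supplement. If the identity-link model does not converge, apply the same term in the marginal logistic model, in line with the fallback in 3.7.1.

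State that any claim that the effect changed will rest on the trend test and not on which rows cross 0.05. State also that power is modest, so a non-significant result is not evidence of a constant effect. Dropping the per-duration p-value columns is optional; the estimates and intervals should stay.

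The cost is one extra model and a few sentences, with no new data. The price of the 1-df choice is that it targets steady growth or decline; the 5-df test covers other shapes with less power against a steady trend.
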